### Random allocation and blinding

After providing their written consent, patients are randomly allocated in a 1:1 ratio to the intervention or control group (A or B). Patients will be randomized through a stratified sequential randomization plan generated online. Randomization will be stratified by disease severity (Acute Physiology and Chronic Health Evaluation (APACHE) II,^1^ 0–35 and 35–70). For allocation concealment, we will use sealed opaque envelopes; inside each there is a carbon paper and the A or B card. To avoid probable selection bias, we will write the patient’s name on the envelope before opening it. All patients, researchers, and medical staff will be blinded to the allocation to either synbiotic or placebo capsules. An available third party, the secretary of the ICU, will be aware of whether A or B is allocated the synbiotic supplement. In the case of any complication associated with the intervention allocated, the medical staff will refer to the secretary for details.

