## Study interventions

### Interventions, administration, and duration

All eligible patients will receive standard hospital gavage as EN through the NGT in the 24-48 h after admission to the ICU. According to the recent European Society of Parenteral and Enteral Nutrition (ESPEN) guideline on clinical nutrition in the ICU [26], continuous rather than bolus EN is preferred because it causes less diarrhea, but there is no difference in other outcomes. Another systematic review showed that bolus feeding is associated with lower aspiration rate and better calorie attainment [27]. It also provides a greater stimulus for protein synthesis [28]. Considering these data and the availability of bolus EN in our hospitals we applied this method. In the absence of an indirect calorimeter, the simple weight-based equation of 20–25 Kcal/kg/day in the acute flow phase and 25–30 Kcal/kg/day in the anabolic flow phase is preferred for measurement of calorie requirements. For overweight and obese patients, ideal body weight: 0.9 × height (cm) − 100 (male) (or − 106 (female) is suggested as a reference weight [26]. To avoid overfeeding, the EN target will be prescribed within 3 days in patients with high nutritional risk and within 7 days in patients with low nutritional risk according to the modified Nutrition Risk in Critically Ill (NUTRIC)^2^ score. The flow charts in Figs. 2 and 3 will be used for initiation and continuation of EN.

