### Description of evaluations

As shown in Fig. 2, calorie achievement goals are set according to the patients’ modified NUTRIC score. In everyday visits, we will evaluate GI signs and symptoms (e.g. vomiting, diarrhea, abdominal distention) and gastric residual volume (GRV). If there is no sign or symptom of intolerance and GRV is less than 250 ml, EN will be increased by 10%. Otherwise, we will approach as shown in Fig. 3. Energy homeostasis (calorie intake-estimated calorie requirement) will be recorded each day. Mid-arm circumference, which is an available anthropometric measurement tool, will be evaluated twice a week. As all patients receiving EN should be monitored for some clinical and laboratory variables, we set our monitoring approach as reported by Berger MM, et al. [34], Monitoring nutrition in the ICU, Clinical Nutrition (2018). Concomitant medications, pressure ulcers, infectious complications, and other adverse events will be recorded every day. The APACHE II and Sequential Organ Failure Assessment (SOFA) will be scored on days 0, 8, and 15. Before and after the intervention, fasting blood and 24-h urine samples will be obtained. Urine urea nitrogen, 3-Methyl histidine, and creatinine will be measured in urine samples. Fasting blood glucose, insulin, C-reactive protein (CRP) and endotoxins will be measured in fasting blood samples.

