### Outcomes

#### Primary outcomes

The primary outcomes are
Energy homeostasis (calorie intake-estimated calorie requirement)Protein catabolism (nitrogen balance)
Nitrogen balance is a measure of the net change in total body protein. It is the difference between nitrogen eliminated from the body and nitrogen ingested in the diet. A positive or neutral nitrogen balance shows that protein stores are increased or maintained, while a negative nitrogen balance indicates protein mass is decreasing. The practical method for estimating nitrogen balance supposes that total nitrogen loss is equal to urinary urea nitrogen excretion plus 4 g/day additional loss from non-urinary urea nitrogen, gastrointestinal, and insensible losses [36, 37]. To measure the nitrogen balance, during the 24-h urine collection, the total intake of protein will be recorded to calculate nitrogen intake: 24-h urine samples will be immediately delivered to the laboratory to measure urea nitrogen.
3.Muscle protein degradation (3-methyl histidine (3MH) in 24-h urine)
3MH is exclusively found in muscle proteins, and after protein degradation, it is rapidly excreted in the urine without further reutilization or metabolization. So, measuring urinary 3MH, after at least 1 day of a meat-free diet, can be used as a biomarker of muscle protein breakdown [38, 39]. After a 1-day meat-free diet, 24-h urine will be collected. Urine samples will be centrifuged for 20 min at 1000×g. The supernatant will be collected and stored at − 70 °C for a maximum of 2 months. The ELISA method will be used for 3MH detection.
4.Muscle protein turnover (3MH/creatinine ratio in 24-h urine)
Since 24-h urinary creatinine estimates the total pool of muscle proteins, muscle protein turnover can be calculated from the 3MH/creatinine excretion ratio [38]. A 24-h urine sample will be delivered to the laboratory to immediately measure creatinine by the enzymatic method.
5.Lipolysis (free glycerol in serum)
Free glycerol is an important index of lipid metabolism. When the body uses stored fat as the energy supply, glycerol and fatty acids are released into the circulation. The absence of glycerol kinase in the adipocyte decreases triacylglycerol resynthesize and supports hepatic gluconeogenesis [40]. After obtaining the overnight fasting blood sample, the serum will be separated. The serum sample will be stored at − 70 °C for further measurement of free glycerol by enzymatic colorimetric method.

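### The energy-balance primary outcome includes a scheduled early deficit that differs by baseline NUTRIC class; adjusting for that class would recover precision

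*Protocol article*

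**What the plan says.** - **Outcome.** Primary outcomes lists energy balance first. Description of evaluations adds: "Energy homeostasis (calorie intake-estimated calorie requirement) will be recorded each day". Table 1 schedules it before the intervention and on days 1 to 15.
- **Reference.** Under Interventions, administration, and duration, the requirement is "the simple weight-based equation of 20–25 Kcal/kg/day in the acute flow phase and 25–30 Kcal/kg/day in the anabolic flow phase". It depends on weight and metabolic phase. It has no term for feeding day or nutritional risk.
- **Feeding rule.** The same section, giving avoidance of overfeeding as the reason, says "the EN target will be prescribed within 3 days in patients with high nutritional risk and within 7 days in patients with low nutritional risk", with risk taken from the modified NUTRIC score. Description of evaluations confirms that "calorie achievement goals are set according to the patients’ modified NUTRIC score".
- **Steps.** Feed is raised in 10% steps when there is no intolerance and gastric residual volume is below 250 ml. Otherwise Fig. 3 applies.
- **Allocation and analysis.** Random allocation and blinding says "Randomization will be stratified by disease severity", using two APACHE II bands. Data analysis lists t tests and repeated-measures ANOVA, and says in general terms that covariates will be handled by ANCOVA or logistic regression. It ties no covariate to energy balance.

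**The concern.** The outcome compares intake with the full requirement from the first day, while the feeding rule allows intake to stay below that requirement for the first days. The length of that period depends on a score fixed at baseline. Part of each patient's result is thus predictable before the first capsule is given and would be there whichever capsule it was.

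At stake is precision in a trial of 40 patients. If a baseline class explains a visible share of the spread in a primary outcome and is left out of its analysis, the arm comparison is noisier than it need be. A chance excess of low-risk patients in one arm then moves the estimate.

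**Working it through.** **Inputs from the protocol:** target reached within 3 days (high risk) or 7 days (low risk), 14 treatment days, 20 patients per arm.

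**Assumptions, because the protocol gives no figure:** the shape of the build-up (Fig. 2 is not available here), a requirement of 1500 kcal/day, a residual SD of 200 kcal/day, half the patients high-risk, and every prescribed kilocalorie delivered. The protocol states no energy-deficit figure to reproduce. Its sample size rests on ICU stay and enters here only as the number per arm.

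**Step 1: scheduled deficit.** Sum over days of (1 − scheduled fraction of requirement), in days of requirement. T is the target day (3 or 7) and d the study day. The last column is difference × 1500 / 14.

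| Build-up assumed | High risk | Low risk | Difference | Ratio | kcal/day in 14-day mean |
|---|---|---|---|---|---|
| d/T | 1.0 | 3.0 | 2.0 | 3.0 | 214 |
| (d−1)/T | 2.0 | 4.0 | 2.0 | 2.0 | 214 |
| Continuous line from 0 | 1.5 | 3.5 | 2.0 | 2.33 | 214 |
| 25% on day 1, linear to 100% on day T | 1.125 | 2.625 | 1.5 | 2.33 | 161 |
| 50% on day 1, linear to 100% on day T | 0.75 | 1.75 | 1.0 | 2.33 | 107 |
| Steps of 10 points of target, ending on day T | 0.3 | 2.1 | 1.8 | 7.0 | 193 |
| Compounded 10% steps, ending on day T | 0.26 | 1.65 | 1.38 | 6.2 | 148 |
| d/T counted from admission, study day 1 = ICU day 2 | 0.33 | 2.14 | 1.81 | 6.4 | 194 |
| d/T counted from admission, study day 1 = ICU day 3 | 0 | 1.43 | 1.43 | undefined | 153 |

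The ratio is unstable. The difference stays between 1 and 2 days of requirement, and it is the difference that drives the variance.

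**Step 2: added variance.** If class is ignored, the variance of the arm difference is multiplied by 1 + gap² × p(1 − p) / SD², with p = 0.5 and SD = 200:
- gap 107: 1 + 107² × 0.25 / 200² = 1.07
- gap 161: 1 + 161² × 0.25 / 200² = 1.16
- gap 214: 1 + 214² × 0.25 / 200² = 1.29

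In effective sample size, 40 / 1.07 ≈ 37 and 40 / 1.29 ≈ 31, a loss equivalent to about 3 to 9 of the 40 patients.

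**Step 3: chance imbalance.** If one arm has 4 more low-risk patients than the other, the arm difference shifts by (4/20) × gap: about 21 kcal/day at 107 and 43 kcal/day at 214. An imbalance of 4 or more has probability about 0.27 if each patient's class is random with p = 0.5, or 0.34 if exactly 20 of the 40 are high-risk. For scale, the standard error of the arm difference is 200 × √(2/20) ≈ 63 kcal/day.

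**Step 4: dependence on the summary analysed.** The between-arm comparison in a repeated-measures ANOVA works on patient means over days, so the 14-day mean is a fair stand-in for a listed method. The protocol does not fix the summary, however. By day 15 both target dates have passed, so a day-15 value carries no scheduled component.

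**The case against.** **Intake minus requirement is a legitimate outcome.** The primary objective is energy and macronutrient homeostasis, and feeding tolerance is a separate secondary outcome. A true deficit counts whatever its cause. This stands: the outcome is not wrongly defined, and scoring against the scheduled goal would answer a different question.

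**Build-up days still carry information.** Feed is raised only when it is tolerated, so early intake partly reflects tolerance. This also stands. A reader might infer that these days show nothing but the schedule; that is true only of a patient with perfect tolerance.

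**There is no bias, and chance imbalance is already in the standard error.** This is correct. The 43 kcal/day shift is less than one standard error, and type I error is unaffected. What remains is avoidable loss of precision.

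**Covariates are usually left to the analysis plan.** That plan may exist, and the general ANCOVA sentence leaves room for this one. The absence of a covariate list is therefore no fault. The point rests on two rules that the article does state, and on what they imply together for one primary outcome.

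**Conclusion.** The point holds as an opportunity to gain precision, not as an error that invalidates the outcome. The scheduled early deficit is larger in low-NUTRIC patients by about 1 to 2 days of requirement, which is 107 to 214 kcal/day in a 14-day mean at 1500 kcal/day. Leaving class out costs about 7% to 29% in variance at a residual SD of 200 kcal/day with half the patients high-risk, and nothing if only a late value is analysed. Letting the gap run from 107 to 286 kcal/day (the top being 2 × 2000 / 14) and the SD from 150 to 300 widens the range to about 3% to 91%, but the top needs a 2000 kcal requirement, a start from zero and the smallest SD together.

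Two stronger readings are not supported. A reader might infer that the low-risk deficit is three times the high-risk one. That ratio belongs to one assumed build-up; others give about 2 to 7, and the 3- and 7-day limits are upper bounds, not fixed schedules. A reader might also infer that the trial is biased. The feeding rule is the same in both arms, so it is not.

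**What to change.** Leave the feeding schedule and the definition of the outcome unchanged. State, before unblinding, that the analysis of energy balance includes baseline modified NUTRIC risk class (high or low) as a covariate. If daily values are modelled, add its interaction with day, because the class difference lies in the build-up days and disappears afterwards.

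Table 1 already schedules the score before the intervention, so nothing new is collected. The cost in a comparison of patient means is one degree of freedom (38 to 37 with 40 patients). The interaction uses further within-patient degrees of freedom. If the real build-up gives a gap near the lower end, the net gain will be small.

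Scoring against the scheduled goal on build-up days is at most an optional supportive analysis. It would need a day-by-day goal for each patient, which neither Table 1 nor the text lists as recorded, and it should not replace the primary outcome.

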**Fig. 2 Fig2:**
[figure not shown]
Flow chart for EN initiation and goal achievement. Abbreviations: EN, enteral nutrition; GRV, gastric residual volume; ICU, intensive care unit; ml, milliliter; NUTRIC, Nutrition Risk in Critically Ill

**Fig. 3 Fig3:**
[figure not shown]
Flow chart of GRV management. Abbreviations: EN, enteral nutrition; GRV, gastric residual volume; ICU, intensive care unit; ml, milliliter; NUTRIC, Nutrition Risk in Critically Ill; SPN, supplementary parenteral nutrition

In the intervention group, patients will receive Lactocare (ZistTakhmir) capsules 500 mg every 12 h for 14 days. Each capsule contains *Lactobacillus casei* 1.5 × 10^9^ colony-forming units (CFU), *Lactobacillus acidophilus* 1.5 × 10^10^ CFU, *Lactobacillus rhamnosus* 3.5 × 10^9^ CFU, *Lactobacillus bulgaricus* 2.5 × 10^8^ CFU, *Bifidobacterium breve* 1 × 10^10^ CFU, *Bifidobacterium longum* 5 × 10^8^ CFU, *Streptococcus thermophilus* 1.5 × 10^8^ CFU, and fructooligosaccharides (FOS). The probiotics capsule will be given through the NGT, separately from gavage, after feeding. Patients in the control group will receive a placebo capsule, which contains only sterile maize starch and is similar to probiotic capsules. The liquid preparations ready for gavage through the NGT are also similar in color and odor.

### Handling of the study intervention

The pharmaceutical company will provide synbiotic and placebo capsules in distinct boxes identified as A or B. Synbiotic capsules can be stored at room temperature for 2–3 weeks but the best condition for keeping this product is in the refrigerator at 2–8 °C. Unused study products will be returned to the company supplying them.

### Concomitant interventions

Concomitant interventions will be:
Antibiotics
It is common that patients under critical care receive at least one antibiotic during their ICU stay. On the other hand, it is believed that antibiotics have bacteriostatic or bactericidal effects on both pathogenic and non-pathogenic bacteria. So, it is recommended that probiotic and antibiotic administration be separated by at least 2 h hours [29].
2.Opioids
Considering their analgesic and sedative properties, opioids are widely used in patients under critical care. Opioids are believed to suppress the immune system and delay GI peristalsis [30]. Delayed peristalsis can increase bacterial translocation out of the GI tract [31].
3.H2 receptor blockers
Prevention of GI tract (GIT) stress ulcers, through H2 receptor blockers or proton-pump inhibitors, is common in critical care practice. Increase in GI acidity can cause overgrowth of some pathogenic bacteria [32].
4.Catecholamines
It is believed that the elevated level of catecholamines in patients under critical care, as prescribed exogenously beside endogenous production, can impair the immune system [33].

These drugs are routinely administered in critical care practice, so we will record and consider them as conflicting factors.

### Adherence assessment

As the researcher will administer the capsules to the patients through the NGT, adherence assessment is not required.

## Study procedures

### Schedule of evaluations

The schedule of evaluations is shown in Table 1.

**Table 1 Tab1:** Schedule of enrollment, intervention, and assessments in accordance with the Standard Protocol Items: Recommendations for Interventional Trials (SPIRIT) guidelines

Study period																	
	Enrollment	Allocation	Post-allocation														Close- out
Time point	Pre- allocation	Pre- intervention	1	2	3	4	5	6	7	8	9	10	11	12	13	14	15
Enrollment																	
Informed consent form	×																
Eligibility	×																
Demographics	×																
Intervention			×	×	×	×	×	×	×	×	×	×	×	×	×	×	
Assessments																	
APACHEII, Modified NUTRIC, SOFA		×								×							×
GCS and vital signs		×	×	×	×	×	×	×	×	×	×	×	×	×	×	×	
Energy homeostasis		×	×	×	×	×	×	×	×	×	×	×	×	×	×	×	×
Abdominal examination		×	×	×	×	×	×	×	×	×	×	×	×	×	×	×	
Fluid balance examination		×	×	×	×	×	×	×	×	×	×	×	×	×	×	×	
GRV																	According to Fig. 3.
Mid-arm circumference		×	×			×			×			×			×		×
Infectious events		×	×	×	×	×	×	×	×	×	×	×	×	×	×	×	×
Pressure ulcer		×	×	×	×	×	×	×	×	×	×	×	×	×	×	×	×
Mg, P, Na, K, Cl		×	×	×	×	×	×	×	×	×	×	×	×	×	×	×	
Glucose		×	×	×	×	×	×	×	×	×	×	×	×	×	×	×	×
Insulin		×															×
AST, ALT,TG, Urea		×				×			×			×			×		
PreAlb		×								×							×
Outcomes		×															×
Concomitant medication		×	×	×	×	×	×	×	×	×	×	×	×	×	×	×	
Adverse events		×	×	×	×	×	×	×	×	×	×	×	×	×	×	×	
Mortality rate																	After 28 days

*Abbreviations*: *ALT* alanine aminotransferase, *AST* aspartate aminotransferase, *APACHE II* Acute Physiology and Chronic Health Evaluation II, *Cl* chloride, *Cr* creatinine, *GCS* Glasgow coma scale, *GRV* gastric residual volume, *K* potassium, *Mg* magnesium, *Na* sodium, *NUTRIC* Nutrition Risk in Critically Ill, *P* phosphorus, PreAlb pre-albumin, *SOFA* sequential organ failure assessment, *TG* triglyceride

### Description of evaluations

As shown in Fig. 2, calorie achievement goals are set according to the patients’ modified NUTRIC score. In everyday visits, we will evaluate GI signs and symptoms (e.g. vomiting, diarrhea, abdominal distention) and gastric residual volume (GRV). If there is no sign or symptom of intolerance and GRV is less than 250 ml, EN will be increased by 10%. Otherwise, we will approach as shown in Fig. 3. Energy homeostasis (calorie intake-estimated calorie requirement) will be recorded each day. Mid-arm circumference, which is an available anthropometric measurement tool, will be evaluated twice a week. As all patients receiving EN should be monitored for some clinical and laboratory variables, we set our monitoring approach as reported by Berger MM, et al. [34], Monitoring nutrition in the ICU, Clinical Nutrition (2018). Concomitant medications, pressure ulcers, infectious complications, and other adverse events will be recorded every day. The APACHE II and Sequential Organ Failure Assessment (SOFA) will be scored on days 0, 8, and 15. Before and after the intervention, fasting blood and 24-h urine samples will be obtained. Urine urea nitrogen, 3-Methyl histidine, and creatinine will be measured in urine samples. Fasting blood glucose, insulin, C-reactive protein (CRP) and endotoxins will be measured in fasting blood samples.

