## Statistical considerations

### General design issues

Data will be analyzed using the intention-to-treat approach.

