### Sample size and randomization

We did not find any similar study that has evaluated our primary objectives. So, we considered one of the main secondary objectives to estimate the required sample size. Mahmoodpoor and co-workers [35] reported the ICU stay in two study groups as 18.6 ± 8 and 11.6 ± 6.3 days. Considering alpha error of 0.05 and power of 80%, the required sample size allowing for 10% dropout is 20 patients in each group.

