### Data analysis

Data will be analyzed using SPSS for windows version 11.5 and MedCalc Statistical Software version 18.11.3 (MedCalc Software bvba, Ostend, Belgium; https://www.medcalc.org; 2019). Descriptive (frequency, percentage, mean, standard deviation) and inferential analysis (student *t* test, paired sample *t* test, repeated measures analysis of variance (ANOVA)) will be performed. Any covariates will be controlled by ANCOVA or binary logistic regression. All tests will be two-tailed and a *p* value <0.05 will be considered as statistically significant.

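### Several primary outcomes have one closing sample, at day 15, when the plan's own ICU-stay figures put about 70% and 33% of patients out of the ICU, and no rule covers them

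*Protocol article*

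**What the plan says.** - **Sampling** (Description of evaluations): "Before and after the intervention, fasting blood and 24-h urine samples will be obtained". Urea nitrogen, 3MH and creatinine come from the urine; fasting glucose, insulin, CRP and endotoxin come from the blood.
- **Schedule** (Table 1): insulin and the general outcomes row are marked only before the intervention and on day 15. Glucose and energy homeostasis are marked daily. CRP, the neutrophil/lymphocyte ratio, glycerol and endotoxin have no row of their own.
- **Course** (Study interventions): "patients will receive Lactocare (ZistTakhmir) capsules 500 mg every 12 h for 14 days".
- **Sizing** (Sample size and randomization): a cited trial "reported the ICU stay in two study groups as 18.6 ± 8 and 11.6 ± 6.3 days". With 5% alpha and 80% power, "the required sample size allowing for 10% dropout is 20 patients in each group".
- **Eligibility**: the inclusion criteria ask for an expected ICU stay above 14 days; the exclusion criteria bar only an expected stay below 4 days.
- **Analysis**: "Data will be analyzed using the intention-to-treat approach" (General design issues). Data analysis lists the t test, paired t test and repeated measures ANOVA, with ANCOVA or logistic regression for covariates.

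**The concern.** One of the two mean stays used to size the trial ends before the closing sample is due. A patient who dies before day 15 has no closing value, and one who leaves the ICU may have none. This is a single-ICU trial in tube-fed patients. Nitrogen balance needs recorded protein intake during a 24-hour urine collection, and 3MH needs a meat-free day first. Those conditions are hard to reproduce once a patient has left the unit, and the article makes no provision for it.

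The loss would not be random. On the planning assumption, the product itself moves patients out of the ICU sooner. Patients still available on day 15 would then be the slowest recoverers of one arm, set against a broader part of the other. The better the product works on stay, the smaller and more selected the primary comparison becomes.

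The same applies to the daily outcomes if they are analysed by classical repeated measures ANOVA. That method drops any patient who lacks one of the days, which does not fit an intention-to-treat analysis.

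**Working it through.** **Inputs.** ICU stay 11.6 ± 6.3 and 18.6 ± 8 days, two-sided alpha 0.05, power 80%, dropout 10%, 20 per arm (Sample size and randomization; Data analysis). Closing sample on day 15 (Table 1). Assumption: the shorter stay is the synbiotic arm. The article does not label the groups, but its Discussion expects shorter stays with the synbiotic.

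**Step 1: the plan's own sample size.** Pooled SD = √((8² + 6.3²)/2) = 7.20; difference = 18.6 − 11.6 = 7.0; standardised difference = 7.0/7.20 = 0.97. The t-based requirement is 17.6, so 18 per arm, and 18/0.9 = 20. The stated figure reproduces. (The normal approximation gives 17, then 19.)

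**Step 2: share out of the ICU by day t**, Φ((t − mean)/SD).

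| | 11.6 ± 6.3 | 18.6 ± 8 |
|---|---|---|
| Day 15 | Φ(3.4/6.3) = Φ(0.54) = 70.5% | Φ(−3.6/8) = Φ(−0.45) = 32.6% |
| Day 14 | Φ(2.4/6.3) = Φ(0.38) = 64.8% | Φ(−4.6/8) = Φ(−0.575) = 28.3% |
| Day 15, gamma | 74.9% | 36.8% |
| Day 15, lognormal | 77.6% | 37.6% |
| Day 15, normal, study day 1 set 1 to 2 days after ICU admission | 76–80% | 37–42% |

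Across all shapes and time origins tried, the range is about 64–82% and 28–48%.

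**Step 3: worst case for the closing sample.** If nobody is sampled after ICU exit, 20 × (1 − 0.705) = 5.9 and 20 × (1 − 0.326) = 13.5 remain, about 6 versus 13. Deaths in the ICU would need separate counting; the article gives no rate.

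**Step 4: selection bias in that worst case, with no true effect on the outcome.** For a normal variable, the mean standardised stay of those still in the ICU is φ(c)/(1 − Φ(c)), with c from Step 2.
- Shorter-stay arm: 0.345/0.295 = 1.17.
- Longer-stay arm: 0.361/0.674 = 0.54.
- Unrounded difference: 0.635.

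If stay and outcome correlate at ρ within each arm, the expected spurious difference is 0.635ρ. The values of ρ are assumptions; the documents give none. Type I error is from simulation at 20 per arm.

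| ρ | Spurious difference | Type I error |
|---|---|---|
| 0.3 | 0.19 SD | about 6.5% |
| 0.5 | 0.32 SD | about 10% |
| 0.7 | 0.44 SD | about 16–17% |

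**Step 5: the eligibility rules beside the planning figures.** If the inclusion criterion really selects patients who stay beyond 14 days, the ICU-stay figures do not describe this population. If the figures do describe it, the day-15 design puts most of one arm at risk. A treatment effect might explain an average of 11.6 days in the synbiotic arm, but not the 28% of the longer-stay group who are out by day 14. The 4-day exclusion adds a second, much lower threshold for the same quantity.

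**The case against.** **Leaving the ICU is not the same as being unsampled.** Hospital stay is tracked separately, and a ward or end-of-treatment sample is possible. This stands. A reader might infer that 70% and 33% of closing values will be missing; the documents support only shares at risk.

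**The stay figures come from another trial**, not shown to have required an expected stay above 14 days, so actual early exit here could be lower. This stands too, but it moves the conflict to the sample-size section rather than removing it.

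**The 10% allowance belongs to a different endpoint.** It was set for ICU stay, where early discharge is an observed result, not dropout. This stands. For the same reason, a reader might infer that power falls from 81% (18 v 18) to about 46% (6 v 13). That calculation carries the 0.97 standardised difference in ICU stay over to the biomarkers, for which the plan gives no effect size. No power loss can be stated for them.

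**The plan never says that its analysis is complete-case**, and missing-data handling may sit in an analysis plan that is not shown. Its absence is not part of this point. What remains is that classical repeated measures ANOVA and the paired t test, both named in the article, need all or both values.

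**Not every primary outcome is affected.** Glucose and energy balance are daily, so it would be wrong to say that all blood and urine outcomes exist only at baseline and day 15.

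**Conclusion.** The point holds as an unreconciled conflict in the design. Nitrogen balance, 3MH, 3MH/creatinine, insulin and endotoxin, with CRP and probably glycerol, depend on one sample at a time when the plan's own figures put about 70% and 33% of patients out of the ICU (65% and 28% by day 14). This rests on normality and on the shorter stay being the synbiotic arm; other shapes and time origins keep the gap between arms wide.

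Whether this becomes missing data depends on a sampling rule that the article does not give. If early leavers are not sampled, about 6 versus 13 of 20 per arm remain, and the spurious difference is about 0.2 to 0.44 SD for assumed correlations of 0.3 to 0.7. At the low end the type I error stays close to nominal, so serious bias is possible but not shown.

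For daily energy balance, also a primary outcome, the named repeated measures ANOVA does not fit the intention-to-treat statement once patients leave or die early.

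**What to change.** 1. **Reconcile** the inclusion criterion, the exclusion criterion, Table 1 and the ICU-stay figures, so that they describe one population.
2. **Closing sample.** State that closing blood and urine are sought on day 15 in every randomised patient still in hospital, and otherwise on the last feasible day before exit. Record the day, and add a sensitivity analysis limited to day-15 samples. The costs are real: sampling time then differs by arm, which a day term only partly handles; a 24-hour collection after a meat-free day is hard to arrange before an unplanned exit; and the rule reaches only patients not yet treated. Recruitment began in March 2019 and was expected to finish in October 2019, so there may be few of them.
3. **Analysis.** For daily energy balance and other repeated measures, replace repeated measures ANOVA with a linear mixed model (baseline, day, arm, arm-by-day) on all available values. For outcomes with one closing value, use baseline-adjusted ANCOVA in place of t and paired t tests; this does not recover missing closing values. The cost is wording and programming on data already collected.
4. **Deaths.** Add a sensitivity analysis that ranks death before the closing sample as the worst outcome.
5. **Evaluable numbers.** State an expected non-evaluable share for the day-15 outcomes that agrees with the ICU-stay assumption, separate from the 10% used for the ICU-stay endpoint.
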